### Interim analysis

Safety and efficacy analysis will be performed by the statistician of the independent Data Monitoring Committee (DMC) after the first 20 and 40 included patients. This analysis will be based on the available, preliminary, post-surgical outcomes and also includes the number of surgical complications and (serious) adverse events ((S)AE). The DMC can advise on premature termination of the study in case of harmful effects, or superiority, in one of the treatment arms or in case of non-feasibility issues.

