### Sample size

The sample size calculation is based on a success rate of surgery (defined as Engel 1A or 1B at 1 year) in the control group (tailoring based on spikes) of 65 %, and the expected success in the experimental group (HFOs) of 80 %. The resulting margin is 15 %. Using a 1-sided 95 % confidence interval and a non-inferiority limit of 10 %, to acquire an 80 % power we need 39 patients per group. This results in a total of 78 patients. We anticipate that 80 % of the eligible patients will participate in the study.

We expect the potential loss-to-follow-up after the initial intervention to be low. Routine clinical visits to the neurosurgeon and neurologist are scheduled after surgery at 6 to 8 weeks, 6 months and 12 months. Our FU questionnaires coincide with these visits. Inclusions will proceed until the target sample size is achieved to address loss to follow-up. Loss to follow-up can be expected from; 1) withdrawal by the subject from the study during follow-up before the first preliminary outcome determination at 6–8 weeks, and 2) withdrawal from the study during the surgery by the surgeon or dedicated team due to urgent medical or technical issues.

Subjects are replaced if they withdraw from the study during follow-up before the first preliminary outcome determination at 6–8 weeks. Subjects who are withdrawn from the study during the surgery by the surgeon or dedicated team due to urgent medical or technical issues are also replaced.

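### The DMC may advise stopping for superiority after 20 and 40 patients on preliminary outcomes, in a non-inferiority trial sized for one look at 12-month outcome

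*Protocol article*

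**What the plan says.** - **Protocol article, Interim analysis.** The DMC's statistician analyses safety and efficacy "after the first 20 and 40 included patients". On the data used: "This analysis will be based on the available, preliminary, post-surgical outcomes". On the possible consequence: "The DMC can advise on premature termination of the study in case of harmful effects, or superiority, in one of the treatment arms". Non-feasibility is a further ground. No interim significance level or boundary is given.
- **Trial design and Outcomes.** The design is non-inferiority with 1:1 allocation. The primary outcome is Engel class at 1 year, with earlier assessments at 6 to 8 weeks and 6 months.
- **Sample size.** Success rates are 65 % (spikes) and 80 % (HFOs), the limit is 10 points and the confidence interval is one-sided 95 %; "to acquire an 80 % power we need 39 patients per group". No allowance for interim looks is mentioned.
- **Statistical methods.** The final comparison is a one-sided chi-square test with risk ratio and risk difference. Interim looks are not mentioned.
- **Discussion, Considerations.** Superiority was not made the design target because it would need too many patients and more than two centers. Proof of superiority is left to a later, larger trial.

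**The concern.** The early stop concerns a different hypothesis, and largely a different endpoint, from those the trial is built to settle. A chance difference in early seizure status among 20 or 40 patients could end the trial. The 12-month non-inferiority question, and the secondary outcomes on cognition, resected volume and quality of life, would then rest on a small fraction of the planned data. A repeated efficacy look with a right to stop also uses up type I error, and the sample size reserves none for it.

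**Working it through.** **1. The plan's own figure.** For non-inferiority with success rates p1 = 0.65 and p2 = 0.80 and limit 0.10:

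n = (1.645 + 0.842)² × (0.65·0.35 + 0.80·0.20) / (0.15 + 0.10)² = 6.183 × 0.3875 / 0.0625 = 38.3, so 39 per arm.

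This matches the plan exactly (power at 39 is 80.6 %). The same formula at one-sided 2.5 % gives 49. The stated size therefore spends the full one-sided 5 % in one look.

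**2. What superiority would need.** With the same rates, n = 6.183 × 0.3875 / 0.15² = 106.5, so 107 per arm. The looks come at 10 and 20 per arm.

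**3. Which outcomes would be available.** The Abstract plans 78 patients in 3 years including 1 year of follow-up, which leaves about 24 months of accrual. If accrual is even (assumption), that is 78/24 = 3.25 per month.
- Patient 20 then enters at about month 6 and patient 40 at about month 12. If each look follows promptly, the first has no 12-month outcomes and the second about one.
- Trial status reports 10 patients in about 9 months. At that pace patient 20 enters at about month 18, and about 10/9 × 6 ≈ 7 of the first 20 would have reached 12 months.

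On either assumption the first look rests mainly on outcomes other than the primary one.

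**4. Precision if the trial stopped there.** With 65 % success in both arms, the half-width is 1.645 × √(2·0.65·0.35/n):

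| Per arm | Half-width (points) | Observed HFO advantage needed to exclude a 10-point deficit |
|---|---|---|
| 10 | 35.1 | 25.1 |
| 20 | 24.8 | 14.8 |
| 39 | 17.8 | 7.8 |

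The last column is the half-width minus 10.

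**5. Error rate for the trial's own claim.** The article gives no interim level, so the levels below are assumptions. A further assumption is that information is proportional to included patients and that the preliminary outcome equals the final one. The true rates are set at the non-inferiority limit, 65 % against 55 %, with variance 0.2275 + 0.2475 = 0.475. A false claim arises if HFO is called superior at a look or non-inferior at the end.

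At an interim level of 5 %, the standard normal statistic must exceed 1.645 + 0.10/√(0.475/10) = 2.10 at the first look, 1.645 + 0.10/√(0.475/20) = 2.29 at the second, or 1.645 at the end. The correlations are √(20/40), √(20/78) and √(40/78). The binomial columns come from 1,000,000 simulated trials with pooled or unpooled standard errors at the looks.

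| Interim level (one-sided) | Normal | Binomial, pooled | Binomial, unpooled |
|---|---|---|---|
| 0.05 | 6.5 % | 6.5 % | 7.1 % |
| 0.025 | 5.6 % | 5.4 % | 6.2 % |
| 0.01 | 5.2 % | 5.1 % | 5.3 % |
| 0.001 | 5.0 % | 4.9 % | 5.0 % |

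The final test alone gives 4.9 % in the same simulation.

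**6. For comparison only.** If all three analyses tested superiority at one-sided 5 % with equal arms, the total would be 10.6 % (normal) or 10.9 % (binomial at 65 %, pooled standard error).

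**The case against.** The strongest reply is that this is a condensed article. A boundary may well stand in the full protocol, the analysis plan or the DMC charter, none of which is shown. The DMC only advises, and superiority shown on the same endpoint would also imply non-inferiority.

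Much of this stands. The missing boundary is not itself the finding, and the article cannot be read as saying that no adjustment exists. A reader might infer that the false-positive rate about doubles. The documents do not support that: 10.6 to 10.9 % requires an unadjusted 5 % at both looks, which is stated nowhere, and a final superiority claim, which the plan does not make.

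A reader might also count the roughly 16 % chance, with equal arms and the same assumed 5 % level, of crossing for one arm or the other at the two looks. That figure includes stops favoring spikes, which are not false claims for HFOs. Nor does the article say that the looks are unblinded.

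The reply does not cover the rest. The article itself fixes superiority as a ground for stopping and preliminary outcomes as the basis. The implication from superiority to non-inferiority holds only on the same endpoint, and early seizure status is not the 12-month outcome. A boundary in another document would control the error on the interim outcome without curing that mismatch.

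**Conclusion.** The point holds as a mismatch between the interim rule and the trial's objective: superiority instead of non-inferiority, preliminary instead of 12-month outcomes, and 10 or 20 per arm where the plan's own rates would require about 107 for superiority. A stop would leave half-widths of about 35 or 25 points against a 10-point limit.

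The effect on type I error is secondary and cannot be fixed from the article. For the non-inferiority claim it runs from none (about 5.0 % at an interim level of 0.001) to modest (about 6.5 to 7.1 % at an unadjusted 5 %), under the assumptions in step 5. The final one-sided 5 % is taken from the Sample size section, because Statistical methods names a one-sided test without restating the level. The point should be settled before the looks take place; it does not invalidate the design.

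**What to change.** In the Interim analysis section and the DMC charter, choose one of two options:

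- **Preferred:** remove superiority of the HFO arm as a ground for stopping, and keep both looks for harm in either arm and for feasibility.
- **If an efficacy stop is wanted:** allow it only on completed 12-month Engel outcomes and only at one-sided p<0.001 (Haybittle-Peto), and state this level.

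Under either option the final one-sided 5 % test and the 39 per group stand unchanged. The cost is one sentence in each document.

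The downside is that early stopping for a large benefit becomes very unlikely. With complete 12-month data on 20 and 40 patients and true rates of 65 % and 80 %, the chance of crossing p<0.001 at either look is about 2 % with a pooled standard error and about 6 % unpooled. In a 78-patient trial whose Discussion puts feasibility first, little is lost. Worse seizure outcome in the HFO arm can still be acted on under the harm criterion.

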### Randomization

Eligible epilepsy surgery patients and/or parents or caregivers will be informed about this study by the researcher in person, minimally 2 weeks in advance of the surgery. Informed consent is asked on the day prior to the day of surgery. After written consent, the patient will be randomized into the treatment allocation (ALEA version-release 2.2). Stratification for participating site and epilepsy type (extra-temporal versus temporal lobe epilepsy) is performed using block randomization of 2, 4 and 6 patients. The stratification for participation site includes an indirect stratification for age, as in the VUmc only adults and in the University Medical Center Utrecht (UMCU) predominantly children are operated on.

### Blinding

Blinding of the treating physicians and neurosurgeons for treatment allocation is not feasible because of the character of the intervention. Therefore, this is a single-blinded trial as patients will be blinded for the treatment allocation to avoid bias of the follow-up results. To guaranty the blinding of the patient, the outpatient physicians, neurologist and psychologist involved in the follow-up procedures are blinded for the ioECoG report during the entire period of follow-up. After study completion or termination patients who wish so will be de-blinded.

### Statistical methods

The primary “intention-to-treat” analyses at study completion are based on the difference between the treatment arms with respect to surgical outcome after 12 months. The primary outcome is a categorical outcome, seizure freedom versus seizure recurrence. Risk ratios (RR) and risk difference with 95 % confidence interval will be calculated (*X*^2^- test, 1-sided). Secondary outcomes are the amount of tissue resected, neurological deficits, duration of surgery, complications, cognition and quality of life. For the secondary outcome parameters consisting of continuous variables, a *T*-test with 95 % confidence interval is calculated and tested (1-sided). For the secondary outcome parameters consisting of categorical variables, the RR and risk difference with a 95 % confidence interval are calculated and tested using a Chi-square test (1-sided). Logistic regression analysis will be performed: 1) to adjust for the stratification factors, by including site and epilepsy type as variables in analysis, and 2) to investigate if there are relations between seizure outcome and subject variables, such as age, gender, and pathology, or with experimental variables, such as the operating surgeon and the amount of anesthesia received. Note that we are not going to use a mixed model to adjust for site, as we consider two sites too small a sample to be representative for other sites. Regression analysis is also performed between seizure outcome and the secondary outcome parameters.

In the logistic regression analysis we will, after screening of the number of missing data, perform multiple imputation. For the primary and secondary endpoint no imputation will be performed. Statistical analysis will be performed in SPSS version 21 (SPSS Inc., Chicago, IL, USA) or higher and/or R version 3.1 or higher.

The number of eligible patients withholding consent will be registered, and demographic information will be collected anonymously for post-hoc explorative analysis to understand potential bias in study outcomes.

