## Methods

### Trial design

“The HFO Trial” is a single-blinded randomized controlled Dutch multi-center clinical trial. This trial is based on a non-inferiority design with an allocation ratio of 1:1. We chose a non-inferiority design, as we considered the primary objective of the study, to demonstrate that the intra-operative prospective use of HFOs to tailor surgery is feasible and will not lead to worse outcome than the widely applied method based on spikes. Secondary objectives of this study are to investigate whether the HFO-based, compared to spike-based, tailoring will lead to differences in the volume of resected tissue, neurologic deficits, surgical duration and complications, cognition and quality of life.

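### The primary analysis names a one-sided chi-square test and never uses the 10-point non-inferiority limit on which the trial was sized

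*Protocol article*

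**What the plan says.** The Trial design section of the protocol article states: "This trial is based on a non-inferiority design with an allocation ratio of 1:1".

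The Sample size section assumes a success rate "in the control group (tailoring based on spikes) of 65" % and "the expected success in the experimental group (HFOs) of 80" %. It then gives the rule for the calculation, "Using a 1-sided 95 % confidence interval and a non-inferiority limit of 10" %, and the result, "to acquire an 80 % power we need 39 patients per group". The total is 78.

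The Statistical methods section describes the primary intention-to-treat analysis of seizure freedom at 12 months. It plans a risk ratio and a risk difference, for which a 95 % "confidence interval will be calculated (*X*^2^- test, 1-sided"). It does not mention the 10 % limit, a null hypothesis shifted by that limit, or which bound of the interval is compared with what. The categorical secondary outcomes, which have no limit, are given essentially the same analysis. The limit appears only in the Sample size section.

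**The concern.** The article sizes the trial for one decision rule and names a different test for the analysis.

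- **The test.** The null hypothesis of an ordinary chi-square test is that the two success rates are equal. Made one-sided, it asks whether HFO tailoring is better (or worse) than spike tailoring. The non-inferiority null is that HFO tailoring is at least 10 points worse, and this test does not address it. Nothing in the section suggests a shifted null, since the same test serves secondary outcomes that have no limit.
- **The interval.** The Sample size section says 1-sided 95 %. In Statistical methods the interval is called 95 %, and the word 1-sided stands next to the test. It could be read as either a 1-sided or a two-sided interval.
- **The measure.** A risk ratio and a risk difference are listed side by side. The limit reproduces the sample size only as a risk difference, and no limit is given for the ratio.

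At stake is the single primary conclusion of the trial. The possible readings can disagree on the same data and have very different power, so the rule should be fixed in the text before outcomes are analysed.

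**Working it through.** **Inputs**, all from the Sample size section: control success 0.65, HFO success 0.80, limit 0.10, one-sided alpha 0.05, power 0.80, 39 per group. The 10 % limit is read as an absolute risk difference, an assumption supported by step 1.

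**1. Reproducing the stated sample size.** With unpooled variance,

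n = (z₀.₉₅ + z₀.₈₀)² × [p_C(1 − p_C) + p_T(1 − p_T)] / (p_T − p_C + limit)²

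= (1.645 + 0.842)² × (0.65 × 0.35 + 0.80 × 0.20) / (0.15 + 0.10)²

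= 6.183 × 0.3875 / 0.0625 = 38.3, rounded up to 39.

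The stated figure is reproduced.

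**2. Power of the Sample size rule** (1-sided 95 % lower bound above -10 points). The standard error at 39 per group is √(0.3875/39) = 0.0997, and 0.25/0.0997 = 2.508. Power = Φ(2.508 − 1.645) = Φ(0.863) = 80.6 %. Exact binomial enumeration gives 81.4 % with a Wald interval and 80.8 % with a Newcombe interval.

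**3. Power if the interval is read as two-sided 95 %.** Φ(2.508 − 1.960) = Φ(0.548) = 70.8 % (exact: 71.0 % Wald, 70.4 % Newcombe). For 80 % power, n = (1.960 + 0.842)² × 0.3875/0.0625 = 48.7, that is 49 per group or 98 in total.

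**4. Power of the one-sided chi-square of equality.** The pooled rate is 0.725, so the null standard error is √(2 × 0.725 × 0.275/39) = 0.1011. Power = Φ[(0.15 − 1.645 × 0.1011)/0.0997] = Φ(−0.164) = 43.5 % (exact enumeration 44.4 %). For 80 % power, 109 per group would be needed.

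**5. The rules are different tests.** If both true rates are 65 %, the chi-square for superiority succeeds in about 5 % of trials. The non-inferiority rule in step 2 succeeds in about 24 %: Φ(0.10/0.1080 − 1.645) = Φ(−0.719) = 23.6 % (exact Wald 24.6 %).

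**6. The same data under each rule.** Take 29/39 successes with HFOs and 25/39 with spikes. The difference is +10.3 points, with standard error 10.4 points (Wald).

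| Rule | Result | Conclusion |
|---|---|---|
| 1-sided 95 % lower bound against -10 | 10.3 − 1.645 × 10.4 = -6.8 | Non-inferior |
| Two-sided 95 % lower bound against -10 | 10.3 − 1.960 × 10.4 = -10.1 | Not shown |
| One-sided chi-square of equality | z = 0.98 (critical value 1.645) | Not significant |

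**The case against.** The strongest reply is that the rule can be recovered by reading the sections together. Statistical methods does plan a risk difference with a confidence interval, the quantity that non-inferiority needs, and introduces the primary analysis as one of the difference between arms. Trial design states the design, and Sample size supplies the limit and the 1-sided 95 % level. This stands. With that level carried over, the planned interval tests the limit with 80.6 % power. It would therefore be wrong to say that the plan as a whole cannot test non-inferiority, or that the trial is too small under its own assumptions. The 71 % and 44 % figures belong to particular readings of Statistical methods. On sidedness, 1-sided is at least as natural a reading as two-sided.

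A second reply is that a journal article may leave the decision rule to a fuller document. That holds for the interval method and similar detail. It does not cover the test, because the article chose to name one, and that test does not match its design. A fuller document with the right rule would differ from this text.

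A reader might also infer that a non-significant chi-square will be taken to show that HFO tailoring is no worse. Under that misuse, a treatment truly 10 points worse (55 % versus 65 %) would pass in about 78 % of trials. The article nowhere proposes this. Its Discussion treats a non-significant finding as what might follow from an overestimated HFO success rate in too small a population, not as evidence of equal performance. The 78 % is a hypothetical and carries no weight here.

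**Conclusion.** The point holds as a mismatch between two sections of the article. Sample size sets a non-inferiority rule, and 39 per group is right for it. Statistical methods names a test of equality, leaves the sidedness of the interval unclear and never refers to the limit. The named test is a misstatement, not only an omission.

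At 39 per group and 65 % versus 80 %, power is 80.6 % for the Sample size rule, about 71 % for a two-sided 95 % bound and about 44 % for the chi-square of equality. Only the first delivers the stated 80 %. These figures assume the article's own success rates, a limit on the absolute risk-difference scale, and outcomes available for all 39 patients per group.

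The conclusion goes no further than that. The sample size is not in error, and the planned risk-difference interval becomes the right primary analysis once it is tied to the limit.

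**What to change.** In Statistical methods, replace the sentence on the primary test with wording such as: *Non-inferiority will be concluded if the lower limit of the 1-sided 95 % confidence interval (equal to the lower limit of the two-sided 90 % interval) for the risk difference in seizure freedom, HFO minus spikes, lies above -10 percentage points. The risk ratio and the chi-square test are supportive or descriptive and do not decide non-inferiority.*

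The cost is a change of wording in one section. It needs no further patients or data, and the total of 78 stands.

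A later test of superiority and the choice of interval method are optional and not part of this correction. The two methods checked under the Sample size rule, Wald and Newcombe, both give exact power of about 81 %.

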### Interventions

Participating patients who will undergo ioECoG-tailored surgery will be randomized into an HFO-guided (arm 1) or standard epileptiform spikes-guided (arm 2) resection.

The ioECoG is routinely recorded at a sampling frequency of 2048 Hz using clinical electroencephalogram (EEG) software. A dedicated HFO team, including two experienced HFO observers, will perform the analysis during surgery when the patient has been allocated to the HFO arm. The HFO reviewers need to achieve consensus about the HFOs and distinguish them from artifacts. This team will, together with the clinical neurophysiologist in charge, advise the neurosurgeon on the extent of the tissue to be resected. HFO analysis is performed visually and off-line using Stellate Harmonie Reviewer (v7.0, Montreal, QC, Canada), as this is currently the only clinical EEG software that provides HFO visualization and marking. A split screen modus will be used to simultaneously visualize ripples (settings: finite impulse response (FIR) filter > 80 Hz, gain 5 μV/mm) and fast ripples (settings: FIR filter > 250 Hz, gain 1 μV/mm) at an elongated time interval of 0.4 s/page, according to the settings described in other studies [15, 18, 21, 22]. Based on pilot data, we expect that the visual analysis of HFOs will require 50 % more time compared to the visual analysis of epileptogenic spikes, which usually takes 3 to 5 minutes per recording. This is an intention-to-treat study. HFOs in eloquent regions will not be resected, similar to standard tailoring practice based on spikes. In absence of HFOs, ictiform spike patterns (for definition see introduction) [11] will always be resected, irrespective of treatment allocation. If no HFOs or ictiform spikes are found a planned resection is performed according to size and location of epileptogenic structural lesion(s), similar to standard clinical practice when no spikes could be identified.

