Secondary outcome parameters are:Volume of resected tissue (in cm^3^): the volume of resected tissue is determined by voxel-based volumetrics of the routine pre-surgical and post-surgical 3D whole head T1 magnetic resonance imaging (MRI) scan.Neurological deficits: neurological deficits are assessed by neurological examination and translated into the National Institutes of Health Stroke Scale (NIHSS) before surgery and before hospital discharge after surgery. The cumulated NIHSS score ranges between 0 and 42; a difference of 1 point on the NIHSS scale between the 2 tests is considered clinically relevant. In that case the NIHSS will be repeated at follow-up moments. Additionally, neurological deficits will be classified as “pre-existing” (either improved or aggravated) or as “new” (either anticipated or unexpected).Duration of surgery: post-hoc analysis of duration of surgery (start-stop time neurosurgeon, in minutes) and ioECoG recording time (in minutes).Surgical complications: accounts are kept of the number of (post-) operative complications, such as bleeding, infection, unexpected or aggravated neurological deficits. These events will also be reported as (serious) adverse events ((S)AE).Cognition: comparison of results from pre-operative and 12-month post-operative neuropsychological evaluation. This routine neuropsychological evaluation includes testing of IQ, working memory and processing speed. All tests performed are chosen according to the age of the patient, but report on the same domains. Per domain individual patients’ results will be dichotomized into negative, no, or positive change compared to pre-surgical baseline.Quality of life (QoL): QoL will be determined pre-operatively, and post-operatively after 6 to 8 weeks, and 6 and 12 months using a visual analog scale (VAS) on overall self-perceived quality of life, or by the parents in case of children < 12 years of age.

Data collection, management and storage is done in open source clinical trial software OpenClinica (OpenClinica, LLC, Waltham, MA, USA; www.openclinica.com), managed by the IT division of the Neurology and Neurosurgery Department of the UMC Utrecht. Figure 1 shows the timeline of the study procedures.

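### Every secondary outcome, harms included, is tested one-sided with no stated direction, and the three-class cognition outcome does not fit the test and effect measures assigned to it

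*Protocol article*

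**What the plan says.** All references are to the protocol article.

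- **Statistical methods** lists six secondary outcomes: resected volume, neurological deficits, duration of surgery, complications, cognition and quality of life. Continuous ones get a one-sided t-test with a 95 % interval. For categorical ones, the risk ratio and risk difference with 95 % "confidence interval are calculated and tested using a Chi-square test (1-sided"). No outcome is exempted, and no direction or margin is given for any of them.
- **Trial design** states the secondary objective without direction: to see whether the two ways of tailoring lead to differences in these outcomes.
- **Sample size** explains where one-sidedness comes from, for the primary outcome only: "Using a 1-sided 95 % confidence interval and a non-inferiority limit of 10" %.
- **Outcomes** says that each patient's cognition results, per domain, "will be dichotomized into negative, no, or positive change compared to pre-surgical baseline". That is three classes.
- **Interventions** expects a cost for the HFO arm in reading time: "we expect that the visual analysis of HFOs will require" 50 % more time than the analysis of spikes.

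**The concern.** A one-sided test needs a stated direction and a reason to disregard the other one. For the primary outcome both exist: the question is whether HFO tailoring is worse by more than a margin. No secondary outcome has a margin, and the objective is non-directional.

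Nor does one direction suit all six outcomes. The article hopes for smaller resections and fewer deficits, but expects longer HFO reading. The Discussion (Considerations) says that electrocorticography may lead to reduction or extension of the planned resection, so deficits could move either way. The Background gives safety as part of the trial's purpose, so the harm comparisons matter.

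Two things are at stake. A reported absence of significant difference in complications could come from a test pointed away from harm, or a nominally significant result could come from a direction settled after the data were seen. For cognition, the choice of which classes to merge is open and can decide the conclusion.

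**Working it through.** **1. The plan's own figure.** Inputs from Sample size: success "in the control group (tailoring based on spikes) of 65" %, and "the expected success in the experimental group (HFOs) of 80" %, margin 10 points, one-sided 5 %, power 80 %.

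n per arm = [p1(1−p1) + p2(1−p2)] × (z0.95 + z0.80)² / (margin + p2 − p1)²
= (0.2275 + 0.1600) × (1.645 + 0.842)² / 0.25² = 38.33, rounded up to 39.

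This agrees with the article ("to acquire an 80 % power we need 39 patients per group"). Power at 39 is 80.6 %. The one-sided 5 % level therefore belongs to the primary calculation, which is not in dispute here. The article gives no size or power for any secondary outcome.

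**2. What sidedness does to a harm comparison at 39 per arm.** The article gives no complication or deficit rates, so three pairs are assumed (spike arm v HFO arm). With d the true excess, SE0 the pooled and SE1 the unpooled standard error:

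- two-sided 5 %: Φ[(d − 1.960·SE0)/SE1]
- one-sided 5 % aimed at harm: Φ[(d − 1.645·SE0)/SE1]
- one-sided 5 % aimed at benefit: Φ[(−d − 1.645·SE0)/SE1], the chance of rejecting at all, and then in the wrong direction

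For 10 v 25 %: SE0 = √(2 × 0.175 × 0.825/39) = 0.0860 and SE1 = √((0.09 + 0.1875)/39) = 0.0844, which gives 41 %, 54 % and 0.03 %.

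| Assumed rates | Two-sided 5 % | One-sided, at harm | One-sided, at benefit |
|---|---|---|---|
| 5 v 15 % | 31 % | 43 % | 0.08 % |
| 10 v 25 % | 41 % | 54 % | 0.03 % |
| 10 v 30 % | 60 % | 72 % | 0.003 % |

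**3. Match with the interval.** On a 2×2 table, one-sided 5 % means a chi-square critical value of 2.71, the same as two-sided 10 %. Two-sided 5 % needs 3.84. If the 95 % interval is two-sided, results between 2.71 and 3.84 would be significant on the test while the interval, to a close approximation, still includes no difference. The article does not say whether these intervals are two-sided; the one in Sample size is one-sided.

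**4. Cognition.** Two arms by three classes is a 2×3 table with 2 degrees of freedom (critical value 5.99). The statistic has no direction, and there is no single risk ratio or risk difference until classes are merged. An invented example with 39 per arm, negative/no/positive change 12/15/12 (HFO) v 6/27/6 (spikes), has expected counts 9/21/9 in each arm:

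- Three classes: 4 × 3²/9 + 2 × 6²/21 = 4.00 + 3.43 = 7.43, p = 0.024.
- Negative v rest (12/27 v 6/33): 2 × 3²/9 + 2 × 3²/30 = 2.60, two-sided p = 0.107, risk ratio 2.0, risk difference 15.4 points. HFO tailoring looks worse.
- Positive v rest: the same counts and so the same figures, but now HFO tailoring looks better.

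The choice of split thus changes both the significance and the clinical direction.

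**The case against.** **The direction is not stated, so it cannot be assumed to be benefit.** This is right. A reader might infer that the planned tests cannot detect harm. The article does not support that: aimed at harm, a one-sided 5 % test is more sensitive than a two-sided one (43 to 72 % against 31 to 60 % above). What stands is that the direction is left open.

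**Harm would be seen in other ways.** A two-sided 95 % interval would show an excess in either direction. The Data Monitoring Committee reviews complications and serious adverse events and can advise stopping for harm. Both are real safeguards. But such an interval would not agree with the one-sided test printed beside it, and monitoring during the trial is not the final comparison.

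**Differing directions are not an error in themselves.** One-sided hypotheses can be set per outcome, and the longer reading time is not itself the duration outcome, which is the surgeon's start-stop time and the recording time. That is correct, so the reading time is only an illustration. The article sets no hypothesis per outcome.

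**The cognition analysis can be run.** A 2×3 chi-square test is routine, a risk ratio can be formed for each class, and a rule for merging may stand in an analysis plan not shown. This is fair, and it rules out saying that no analysis is possible. The word for two classes applied to three, and the one-sided label on a test without direction, remain faults of the text itself.

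**Use of baselines.** A reader might also infer that pre-operative scores are ignored. The Outcomes section contradicts this: cognition is classed as change from baseline, and the NIHSS is compared before and after surgery. For the quality-of-life scale the article only leaves open how the pre-operative value enters, which an analysis plan may settle. That is not a fault.

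**Conclusion.** The point holds in two parts.

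1. One-sided testing of all secondary outcomes, without direction or margin, does not fit a non-directional objective and borrows its level from the primary non-inferiority question. Its size depends on the direction: below 0.1 % chance of flagging an excess of harm if aimed at benefit, against 31 to 60 % two-sided; if aimed at harm or chosen later, a nominal level equal to two-sided 10 %. These percentages rest on 39 per arm, the normal approximation and assumed harm rates.
2. Cognition is called dichotomized but has three classes, for which the single risk ratio, the single risk difference and the one-sided chi-square test are undefined. The numerical example is invented and shows only that the split can decide the result.

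Neither part touches the primary analysis or the 39 per arm. An unseen analysis plan could add directions and a rule for merging classes, but one-sided tests would still not fit the objective as written. The change should be made; it is not a threat to the trial's main conclusion.

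**What to change.** - In Statistical methods, replace the one-sided tests of secondary outcomes by two-sided 95 % confidence intervals and two-sided 5 % tests for all secondary and safety outcomes, and say that the intervals are two-sided. Keep one-sidedness for the primary non-inferiority comparison.
- In Outcomes, correct the word dichotomized. Then either prespecify one split, for example decline v no decline, for the risk ratio and risk difference, or keep the three classes and name an ordinal analysis.
- Optional: state the visit at which quality of life is compared and adjust for the pre-operative score.

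The cost is wording: no new data and no change in sample size. The downside is that nominal significance for a benefit becomes slightly harder to reach, with a critical value of 1.960 instead of 1.645. Even two-sided, power for harm is modest at this size, so the estimate and its interval should carry the interpretation.
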